## **Validity of the Trial Implementation.**

If this study demonstrates that salvaged RBC transfusions do not increase blood loss compared with allogeneic RBC transfusions, it could lead to a reduction in the use of allogeneic RBC products and avoidance of adverse effects associated with them, thereby contributing to the maintenance of the blood supply system, medical economics, and ultimately patient benefit.

# **Objective**

This study aims to evaluate, through a single-blind randomized controlled non-inferiority trial, the hypothesis that intraoperative salvaged RBC transfusion for anemia after CPB in high-risk cardiovascular surgery does not result in greater postoperative bleeding compared to a transfusion strategy using only allogeneic RBC

# **Trial Design**

1. Design

- Type of control: Standard treatment control
- Design characteristics: Parallel group comparison
- Randomization: Yes (stratified block randomization)
- Blinding: Single-blind (participant blinded)
- Type of trial: Non-inferiority trial

1. Invasiveness: Yes (exceeds minimal invasiveness)
2. Intervention: Yes
3. Use of samples: New sample are collected
4. Use of information: New information is collected, and existing information is also used

# **Outcomes**

## **Primary Outcome**

Postoperative chest tube blood loss within 12 hours from the end of surgery. If re-thoracotomy for bleeding or hematoma removal is required within 12 hours, the intraoperative blood loss during re-thoracotomy is added to the total for calculation.

## **Secondary Outcomes**

1. Allogeneic RBC transfusion volume during surgery and for 12 hours from the end of surgery
2. Prevalence of re-thoracotomy within 48hours from the end of surgery
3. Prevalence of the postoperative chest tube blood loss within 12 hours from the end of surgery ≥1000mL

### **Safety Outcomes**

1. Prevalence of any of the following infections, defined according to the CDC diagnostic criteria[16]: surgical site infection, mediastinitis, urinary tract infection, respiratory infection, central nervous system infection, gastrointestinal infection, skin and soft tissue infection, etc.
2. Prevalence of gross hematuria upon ICU admission
3. Prevalence of acute kidney injury within 7 days after surgery, defined in accordance with the Kidney Disease: Improving Global Outcomes criteria.[17]

Safety outcomes 2) and 3) are set as indicators of mechanical hemolysis, one of the potential adverse events associated with salvaged RBC transfusion.

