## **Visit 2. Final Registration and Randomization (Baseline)**

The following data are collected up to the time of CPB weaning on the day of surgery.

| 1) Clinical and Laboratory Data**^*2^** | |
| --- | --- |
| Physical findings | Height, weight, body surface area |
| Laboratory tests | White blood cell count, hemoglobin, platelet count, total protein, albumin, total bilirubin, direct bilirubin, AST, ALT, creatinine, LDH, CK, CK-MB, sodium, potassium, chloride, calcium, CRP, PT-INR, APTT, fibrinogen, D-dimer, FDP, ATIII activity |
| 2) Oral Medication Information | |
| Oral medications | Discontinuation period of antiplatelet agents and anticoagulants |
| 3) Surgical Information | |
| Treatment Information | Use of allogeneic RBC transfusion during CPB |

*2 Information are collected prior to the induction of general anesthesia. If results obtained during routine clinical care are available within 14 days before the day of surgery, those results are used.

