## **Visit 3. During Study Treatment**

The following information is collected after weaning from CPB on the day of surgery (allowable range: +3 days). Data isobtained from the anesthesia records (ORSYS) and electronic medical records (MegaOak).

| 1) Study Treatment Information | |
| --- | --- |
| Treatment Information | - Volume of salvaged RBC and transfused allogeneic RBC (a) during from the start of general anesthesia to weaning from CPB, and (b) from weaning from CPB to leaving the operating room - Intraoperative blood loss - Heparin concentration in salvaged RBC (salvaged RBC group only)^*3^ |
| 2) Clinical and Laboratory Data |  |
| Vital signs | Blood pressure, heart rate, peripheral oxygen saturation (SpO₂), central venous pressure, pulmonary artery pressure, cardiac output (at the end of surgery) |
| Physical findings | Gross hematuria upon ICU admission |
| Blood gas analysis | Hemoglobin (at the following time points: after induction of general anesthesia, before initiation of CPB, during CPB, after CPB following protamine administration, and additionally as needed) |
| Laboratory tests | Hemoglobin, platelet count, PT-INR, APTT, fibrinogen, and blood viscoelastic testing (at the following time points: before and after weaning from CPB following protamine administration, at ICU admission, and additionally as needed)  Total protein, albumin, total bilirubin, direct bilirubin, AST ALT, creatinine, LDH, CK, CK-MB, sodium, potassium, chloride, calcium, and CRP (laboratory data collected at the time of ICU and subsequently as required). |
| 2) Concomitant Treatment Information | |
| Concomitant Therapy | - Volume of transfused FFP, platelet concentrates, and cryoprecipitate during (a) from the start of general anesthesia to weaning from CPB, and (b) from weaning from CPB to leaving the operating room - Total intraoperative doses of colloid solutions, tranexamic acid, heparin (excluding that used in the salvage system), and protamine |
| 3) Surgical Information | |
| Surgical Information | Definitive diagnosis, definitive surgical procedure, operative time, CPB time, aortic cross-clamp time, lowest temperature during CPB |
| 4) Adverse Events | |
| AEs | Date of onset, event name, known/unknown, seriousness, severity, causal relationship, treatment, outcome, date of outcome confirmation, other details |

*3 Measured for research purposes

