## **Visit 4. End of Study**

Observations and examinations are performed 30 days after the initiation of study treatment (acceptable range: ±5 days). Data is collected from the critical care information system (AXIS) and electronic medical record system (MegaOak).

| 1) Study Treatment Information | |
| --- | --- |
| Treatment Information | - Postoperative chest tube blood loss within 12 hours after ICU admission - Total chest tube blood loss until removal - Transfusion volume within 24 hours after ICU admission (RBC, FFP, cryoprecipitate, platelet concentrates) - Duration of mechanical ventilation - Length of ICU stay - Postoperative hospital stay - Date of discharge |
| Discontinuation/interruption of treatment | Presence or absence; if applicable, record the date, reason, and subsequent management |
| 2) Clinical and Laboratory Data | |
| Laboratory tests  (obtained on the day after surgery) | White blood cell count, hemoglobin, platelet count, total protein, albumin, total bilirubin, direct bilirubin, AST, ALT, creatinine, LDH, CK, CK-MB, sodium, potassium, chloride, calcium, CRP, PT-INR, APTT, fibrinogen |
| 3) Adverse Event Reports | |
| AEs | Date of onset, event name, known or unknown, seriousness, severity, causal relationship, treatment, outcome, date of outcome confirmation, readmission status (presence/absence), date of readmission, date of discharge, and other relevant details |
| 4) Outcome Information | |
| Survival status | Outcome: alive, deceased, or lost to follow-up  Date of last confirmed survival or date of death; in case of death: cause of death If lost to follow-up: reason for discontinuation of follow-up |
| Stuidu withdrawal | Presence or absence; if applicable, record the date and reason for withdrawal |

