| **Heparin concentration in salvaged RBC**  **(Salvaged RBC group only)** |  |  | ● |  |  |
| **Concomitant treatment information** |  |  | ○ |  |  |
| **Surgery Information** |  | ○ | ○ |  |  |
| **Adverse events** |  |  |  |  |  |
| **Outcome information** |  |  |  | ○ | ○ |

　➡ : Assessed throughout the study period ◎: Mandatory items ○: Routine clinical examination item ●: Study-specific examination

*1 Results obtained from routine clinical care within 90 days before obtaining informed consent may be used for the study.

*2 Information must be collected before the induction of general anesthesia. If results from routine clinical care are available within 14 days before the day of surgery, they are used.

*3 Data obtained on the day after surgery is used.

*4 To be performed whenever possible. If results from other visits or routine clinical care are available within one day prior to the date of study discontinuation, they are used.

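### Acute kidney injury is a 7-day safety outcome, but the last fixed creatinine is on the day after surgery, so cases on days 2 to 7 are not systematically captured

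*Protocol*

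**What the plan says.** Protocol section 4.3 (Safety Outcomes) lists as its third item "Prevalence of acute kidney injury within 7 days after surgery", defined by the KDIGO criteria. The Study Overview repeats it. Section 4.3 also gives the reason: "Safety outcomes 2) and 3) are set as indicators of mechanical hemolysis".

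Creatinine appears in the visit tables as follows.

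- **Visit 2 (baseline, section 8.2):** taken before induction. "If results obtained during routine clinical care are available within 14 days before the day of surgery, those results are used".
- **Visit 3 (section 8.3):** "laboratory data collected at the time of ICU and subsequently as required". No days are named, and the visit has a tolerance of three days after surgery.
- **Visit 4 (section 8.4):** the visit is at day 30 (±5 days), but its laboratory panel is "obtained on the day after surgery". Footnote 3 to the Observation and Inspection Schedule agrees: "Data obtained on the day after surgery is used".

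Urine output is not an item at any visit. The only urine finding listed is gross hematuria on arrival in the ICU. Separately, section 9.4.1 has adverse events reported for at least 30 days from the start of study treatment.

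**The concern.** The outcome runs for seven days, while the schedule fixes postoperative creatinine only at ICU admission and on day 1. A patient whose creatinine first rises on day 3, 5 or 7 becomes a case only if someone happened to test and the result reached the data.

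This outcome is one of two chosen as markers of haemolysis from salvaged red cells. The other is a single look for gross hematuria at ICU admission, so acute kidney injury is the only one of the pair with follow-up beyond that moment. A result reported as 7-day KDIGO injury, but built from day-1 values plus whatever else was ordered, would be labelled as something that was not consistently measured.

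**Working it through.** **Step 1. Window against schedule.** Day 1 is the day after surgery.

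| Outcome day | Creatinine in the visit tables |
|---|---|
| 0 | fixed (ICU admission) |
| 1 | fixed (Visit 4 panel) |
| 2–3 | only as needed, if Visit 3's tolerance is read generously |
| 4–7 | none |

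Six of the seven days after surgery (2 to 7) have no fixed value. Four of them (4 to 7) lie beyond even the as-needed route.

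**Step 2. Other routes into the data.** The adverse event fields in sections 8.3 and 8.4 cover onset date, event name, seriousness, severity, causality, treatment and outcome. Severity (section 9.3.2) is mild, moderate or severe. No field holds a creatinine value or a KDIGO stage. The early-discontinuation panel (section 8.5) applies only to participants who stop early.

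**Step 3. Plan figures.** The protocol gives no rate, power or sample size for acute kidney injury. The only plan figure used below is 71 per group, which was set for drainage volume. It reproduces: n = 2 × (1.960 + 0.842)² × 400² / 200² = 62.8, so 63 per group by the normal approximation, or 64 by the noncentral t distribution (power 0.8015). Then 64 / 0.9 = 71.1, stated as 71.

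**Step 4. Equal capture in both arms.** Let pC and pT be the true 7-day risks (allogeneic, salvaged) and s the share of true cases captured, with no false positives.

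- Observed risks: s·pC and s·pT
- Risk difference: s·(pT − pC), shrunk in proportion to s
- Risk ratio: s·pT / s·pC = pT / pC, unchanged
- Odds ratio: [s·pT / (1 − s·pT)] / [s·pC / (1 − s·pC)], moved toward 1
- Power (two-sided 5%, 71 per group): Φ[(difference − 1.96·SE0) / SE1], with SE0 pooled and SE1 unpooled

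All risks and values of s are assumptions; the protocol supplies none.

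| True risks (pC, pT) | s | Observed risks | Difference (points) | Risk ratio | Odds ratio | Power |
|---|---|---|---|---|---|---|
| 20%, 30% | 1.00 | 20.0%, 30.0% | 10.0 | 1.50 | 1.71 | 28% |
| | 0.75 | 15.0%, 22.5% | 7.5 | 1.50 | 1.65 | 21% |
| | 0.50 | 10.0%, 15.0% | 5.0 | 1.50 | 1.59 | 14% |
| 30%, 45% | 1.00 | 30.0%, 45.0% | 15.0 | 1.50 | 1.91 | 45% |
| | 0.75 | 22.5%, 33.8% | 11.3 | 1.50 | 1.75 | 32% |
| | 0.50 | 15.0%, 22.5% | 7.5 | 1.50 | 1.65 | 21% |
| 20%, 40% | 1.00 | 20.0%, 40.0% | 20.0 | 2.00 | 2.67 | 74% |
| | 0.75 | 15.0%, 30.0% | 15.0 | 2.00 | 2.43 | 57% |
| | 0.50 | 10.0%, 20.0% | 10.0 | 2.00 | 2.25 | 38% |

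**Step 5. Unequal capture.** Assume true risks of 40% (salvaged) and 30% (allogeneic), a difference of 10 points.

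- Capture 0.6 salvaged, 0.8 allogeneic: 0.40 × 0.6 − 0.30 × 0.8 = 0.24 − 0.24 = 0 points.
- Capture 0.8 salvaged, 0.6 allogeneic: 0.40 × 0.8 − 0.30 × 0.6 = 0.32 − 0.18 = 14 points.

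The error can therefore hide a difference or exaggerate one.

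**The case against.** The visit tables are not a closed list of outcome sources. Infections and re-thoracotomy also lack a dedicated field there and must come from adverse event reports or the hospital record. Visit 4 draws on the critical care system and the electronic record, and adverse events are collected with onset dates. Footnote 3 says which results fill the Visit 4 panel; it does not say that kidney injury is judged on them alone. How the outcome is derived may be set out in the statistical analysis plan, which is not at hand.

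Much of this stands. A reader might infer that every late case is missed. The documents do not support that, because a clinically recognised case on days 2 to 7 can be recorded as an adverse event. A reader might also infer that the comparison is biased toward no difference. That too goes further than the documents allow: the risk ratio is unaffected under equal capture, the protocol names no effect measure for this outcome, and unequal capture can push either way. Section 7.4 blinds outcome assessors and postoperative physicians, which makes similar capture plausible. It does not assure it, since blinding may be lifted for uncontrollable bleeding and as-needed testing follows the clinical course. Nor can the absence of urine output be called an error in itself: the protocol cites KDIGO without reproducing its criteria, so the point is only that its use is left unstated.

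What does not stand is leaving the matter to the analysis plan. That document can define a derivation, but it cannot supply values that the schedule does not collect.

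**Conclusion.** The mismatch holds on the protocol alone: a 7-day outcome rests on fixed creatinine that ends at day 1, with nothing fixed on six of the seven days. Late cases are captured unsystematically, and mild rises without clinical recognition are the most likely to be lost. If capture is equal and there are no false positives, incidence and the risk difference are understated by the share of cases lost, and power falls; in the assumed settings above, with half the cases captured, power drops from 28–74% to 14–38%. The risk ratio is unchanged. If capture differs by arm, the direction is unknown. The true loss cannot be estimated from the protocol.

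This should be corrected, but its reach is limited. It concerns one of three safety outcomes and leaves the drainage comparison and the sample size untouched.

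**What to change.** At Visit 4, extract from the hospital systems already in use all routine creatinine values from day 0 to day 7 with their dates, and any start of renal replacement therapy. Grade them against the Visit 2 creatinine. Report by arm how many patients have at least one value on days 2 to 7, so that readers can judge whether capture was similar. State whether the urine-output criterion is applied and, if so, where those data come from.

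If later values will not be extracted, restate the outcome as creatinine-based acute kidney injury up to the last day on which creatinine is collected.

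The cost is a few more CRF fields and some chart extraction, with no extra blood sampling. The limit is that detection of late cases would still depend on routine testing; the by-arm count makes that visible but does not remove it.

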### **Experimental outcomes**

1. Results of blood viscoelastic testing, prothrombin time, activated partial thromboplastin time, and platelet count
2. Transfusion volume during surgery and for 12 hours from the end of surgery (FFP without cryoprecipitate/cryoprecipitate/platelet concentrate)
3. Duration of surgery (hours)
4. Duration of CPB (hours)
5. Duration of postoperative mechanical ventilation (hours)
6. Duration of ICU stay (hours)
7. Mortality (all-cause death and cardiovascular death)
8. Heparin concentration of salvaged RBC after processing remaining blood in the CPB circuit in the cell salvage device
9. Amount of protamine sulfate in the OR and within 12 hours from the end of surgery.

※Cardiovascular death is defined as death caused by the following factors:

1. Sudden cardiac death
2. Heart failure
3. Myocardial infarction
4. Stroke
5. Other cardiovascular-related causes (e.g., aneurysm, pulmonary embolism)

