## **Administration of the Study Treatment**

Consent and provisional registration are completed before the day of surgery. The final registration and randomization occurs during CPB. From the point of CPB weaning (protamine administration), the study product is administered based on the hemoglobin levels.

< Administration criteria for the study treatment>

If hemoglobin is less than 10.0 g/dL or is anticipated to drop below this level, transfusion is administered per group assignment.

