### **Concomintant Therapies**

- FFP: Begin after weaning from CPB. The ratio of FFP to total RBC transfusion volume (salvaged + allogeneic) should not exceed 1:1. If the fibrinogen level is ≥200 mg/dL and there is no bleeding tendency, FFP transfusion should not be administered.
- Cryoprecipitate: If fibrinogen is <100 mg/dL, administer the equivalent of 12 units of FFP. Consider 12 units of FFP if the fibrinogen level is 100–149 mg/dL.
- Tranexamic Acid: Administer a 1 g bolus at the start of surgery, followed by continuous infusion at 2 mg/kg/h until the end of surgery.
- Protamine: Administer 3 mg/kg at CPB weaning. If the clotting time ratio in a blood viscoelastic test (Quantra) is ≥1.2 or ACT exceeds H-ACT (ACT after heparin neutralization), additional doses are required.
- Voluven® (Colloid Solution): Limit the total intraoperative volume to 50 mL/kg.

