### **Post-Treatment**

Within the first 12 hours after ICU admission, the transfusion protocols are as follows:

- RBC Transfusion: Administer allogeneic RBC if hemoglobin level is <10.0 g/dL or is expected to fall below this level. Leftover salvaged RBC should not be transfused. During re-thoracotomy within 12 hours, only allogeneic RBC is used for both groups. After 12 hours, there are no restrictions on the use of salvaged or allogeneic RBC during surgery.
- Platelet Transfusion: Administer if the platelet count is <100,000/μL and clinical bleeding is evident.
- FFP Transfusion: Administer if there is a bleeding tendency with APTT > 50 seconds, PT-INR > 1.3, or fibrinogen < 150 mg/dL. However, if the clotting time ratio is ≥ 1.2, protamine is administered, and the APTT value is reassessed thereafter. In cases of massive bleeding, transfusion is performed in the ICU with a target ratio of total FFP transfusion volume to total allogeneic RBC transfusion volume of approximately 1.
- Protamine: Administered if clotting time ratio ≥1.2 in the Quantra test or if ACT exceeds H-ACT.

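### Experimental outcome 9 counts the fixed 3 mg/kg weaning dose of protamine, which dilutes any arm difference in additional protamine, and its postoperative part has no listed data item

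*Protocol*

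**What the plan says.** Protocol section 4.4 (Experimental outcomes), item 9, is the "Amount of protamine sulfate in the OR and within 12 hours from the end of surgery". It states no purpose, does not set the weaning dose apart and is not expressed per kg.

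Section 7.6.2 (Concomitant Therapies) prescribes, for both arms, "Administer 3 mg/kg at CPB weaning", and continues: "If the clotting time ratio in a blood viscoelastic test (Quantra) is ≥1.2 or ACT exceeds H-ACT (ACT after heparin neutralization), additional doses are required". Section 7.5 (Administration of the Study Treatment) makes the same moment the start of the study-product period: "From the point of CPB weaning (protamine administration), the study product is administered based on the hemoglobin levels". In the ICU, section 7.6.3 (Post-Treatment) has no weight-based dose, only a trigger: "Administered if clotting time ratio ≥1.2 in the Quantra test or if ACT exceeds H-ACT".

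On data collection, section 8.3 (Visit 3) lists "Total intraoperative doses of colloid solutions, tranexamic acid, heparin (excluding that used in the salvage system), and protamine". Section 8.4 (Visit 4) lists postoperative blood products but no protamine, and the observation schedule marks concomitant treatment at Visit 3 only. Body weight is collected at Visits 1 and 2 ("Height, weight, body surface area").

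**The concern.** Outcome 9 adds two quantities of different kinds. The weaning dose is set by body weight under one rule for both arms, at the moment from which study product may first be given. It can therefore carry no information about what the study product does. The additional doses in the operating room and the ICU are given on a clotting-time or ACT trigger, and these could respond to heparin returned with salvaged cells.

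Section 1.4 names residual heparin after washing as the unresolved problem behind the trial. Because protamine is given on these triggers, it could offset a heparin effect before that effect shows as drainage. Similar drainage reached with more additional protamine in the salvage arm would read differently from similar drainage without it. Experimental outcome 8, the heparin concentration, is measured in the salvage group only and gives no comparison between arms. Additional protamine is one of the few between-arm measures that could inform the point, so it is worth measuring without avoidable noise.

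The data items raise a second problem. One intraoperative total cannot be split afterwards, and the ICU doses, which are purely trigger-driven and belong to the outcome, are not listed for collection.

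**Working it through.** **Does the fixed dose fall in the outcome window?** Yes. It is given at weaning (7.6.2), in the operating room, and the outcome counts the whole operating-room amount (4.4).

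**Number of patients.** The Protocol states no figure for outcome 9, so there is none to reproduce. The evaluable number comes from the primary outcome (Study Overview: SD 400 mL, margin 200 mL, α 0.025, β 0.2). The normal approximation gives n = 2 × (400/200)² × (1.960 + 0.842)² = 62.8, so 63 per arm. The t-based solution is 63.8, so 64 per arm, the Protocol's figure of 128 in total. I use 64 per arm.

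**Model.** Total protamine = 3 × weight + additional dose. Taking the two parts as independent:

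- SD of the fixed part = 3 × SD(weight)
- SD of the total = √[(3 × SD(weight))² + SD(additional)²]
- share of variance due to weight = (3 × SD(weight))² / SD(total)²
- difference detectable with 80% power = (1.960 + 0.842) × SD × √(2/64) = 0.495 × SD

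**Assumed inputs.** The Protocol gives none of these. Weight SD is taken as 8 to 15 kg, so the fixed part has an SD of 24 to 45 mg. The additional-dose SD is taken as 10 to 50 mg.

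| SD of additional dose (mg) | Weight share of variance in the total | Detectable difference, total (mg) | Detectable difference, additional doses only (mg) |
|---|---|---|---|
| 10 | 85–95% | 12.9–22.8 | 5.0 |
| 20 | 59–84% | 15.5–24.4 | 9.9 |
| 30 | 39–69% | 19.0–26.8 | 14.9 |
| 50 | 19–45% | 27.5–33.3 | 24.8 |

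The two extremes, written out:

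- Weight SD 8 kg, additional SD 50 mg: 24² / (24² + 50²) = 576/3076 = 19%.
- Weight SD 15 kg, additional SD 10 mg: 45² / (45² + 10²) = 2025/2125 = 95%.

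**Power in one middle case.** With weight SD 10 kg and additional SD 20 mg, SD(total) = √(30² + 20²) = 36.1 mg. For a true difference of 10 mg, power is 35% with the total and 81% with additional doses only. For 20 mg it is 88% and above 99%.

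**Can the fixed part be removed from the data as listed?** Only in part. Total minus 3 × weight recovers the additional operating-room dose if each patient received exactly 3 mg/kg. Any rounding or departure is then counted as additional protamine.

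**Is the postoperative part collected?** Not by any listed item. The Visit 3 protamine item is intraoperative by its own wording, so the +3-day allowance at that visit does not extend it. Visit 4, which draws on the ICU system, has no protamine entry.

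**The case against.** The strongest reply is that this is analysis detail. Section 12 leaves statistics to a separate SAP, which is not shown. Whether an experimental outcome is reported in mg, per kg, net of a fixed dose or adjusted for weight is ordinary SAP content. Nothing in item 9 is false, weight is collected, and the weaning dose follows the Protocol's own rule, so subtraction or adjustment is open. Total protamine is also a legitimate measure of exposure.

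Much of this stands, and it limits the point. It does not remove it. The outcome definition and the data items are fixed in the Protocol, and no SAP can recover a split, or an ICU dose, that was not recorded.

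Three stronger readings are tempting, and the documents do not support them:

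- A reader might infer that body weight swamps the outcome. Across the assumed ranges the weight share runs from a minority (19%) to nearly all (95%), and it dominates only if additional doses vary little.
- A reader might take outcome 9 as the Protocol's declared marker of residual heparin. No purpose is stated, although section 4.3 does say so where outcomes are meant as indicators (gross hematuria and kidney injury for hemolysis). The link is a reasonable inference from sections 1.4, 7.6.2 and 7.6.3. Nor is the trigger specific to salvaged cells: it applies in both arms and would also respond to bypass heparin not fully neutralized. Coagulation and viscoelastic tests (item 1) bear on the same question.
- A reader might fear a biased comparison. Randomization balances weight on average, so only precision is lost.

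**Conclusion.** The point holds as a loss of precision on an experimental outcome, together with a gap in data collection. The primary comparison and its conclusion are unaffected.

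That the fixed dose is inside the outcome, that the operating-room record is a single total and that no postoperative protamine item is listed can all be read directly from the Protocol. The size of the loss cannot. It rests on assumed SDs for weight and additional dose and on their independence. If heavier patients also tend to receive larger additional doses, the SD of the total would exceed the figures above. Additional doses will also be zero for patients who meet no trigger, so the SD-based figures are only a guide to scale. The change is cheap and worth making.

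**What to change.** In section 4.4, define outcome 9 as protamine given after the initial weaning dose, up to 12 hours after surgery ends, in mg and mg/kg. Add the proportion of patients given any such dose. Keep total protamine as a descriptive result, since a departure in the initial dose itself would not show in the additional doses.

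Replace the single protamine item with three:

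- initial weaning dose (Visit 3, from ORSYS)
- additional operating-room doses (Visit 3, from ORSYS)
- ICU doses up to the 12-hour limit (Visit 4, from AXIS)

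Update the observation schedule to match. If the initial dose cannot be separated in the records, adjust the total for body weight, which is already collected.

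The cost is two extra data fields from systems already used as sources, and staff must label which dose was the initial one. Splitting the Visit 3 item alone would not be enough, because the ICU doses would still be missing. No dosing rule changes.
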